## Methods

### Participants

Computer required sample size analysis for repeated measures ANOVA within-between interaction, with an effect size of 0.25 [medium effect size; average from effect sizes in changes by yoga in previous studies (9, 25)], a power of 0.80, an alpha error probability at 5%, for two groups (yoga and comparison) and two measurements (pre-and post-intervention) suggested a sample size of 34 for each sex.

We aim to collect complete data from at least 34 participants of both sexes (34 male and 34 female clients) to perform gender-specific analyses. Gender analyses will only be performed, if this number of participants can be reached.

Based on previous experience working with participants within correctional settings, we know that the attrition rate can reach 50%; therefore, our aim is to include approximately 120 participants.

Three institutions at the South West in Sweden have at this stage declared interest in participating in the study. Data collection is planned to take place for one and a half years' time, based on an estimated three months per institute (Figure 1). This three months period includes spreading advertisements and information about the study, collecting informed consents, six weeks of intervention (including pre- and post-intervention tests), and time for qualitative interviews to assess individual experiences of yoga classes. As the average time spent within SiS is calculated to be eight months, we will be able to perform intervention and data collection in each participating institute twice, six months apart during the planned data collection period (one and a half years) (Figure 1).

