### Data Analysis

If the required number of male and female participants (at least 34 of each gender) is reached, then we will analyze the data separately by gender. Otherwise, the data will be pooled, and no gender-specific results will be presented.

All statistical analyses will be conducted using a significance level of *p* <0.05. Only complete post-attrition data will be analyzed. The comparison of the attrition rates between the two groups (“yoga” group and “comparison” group) will be calculated using Fisher's exact test. The Test 1 and 2 scores within the groups will be compared using the Wilcoxon signed-rank test. Mean changes and standard deviations will be calculated to identify differences within the groups. Mann–Whitney *U-*tests will be used for the continuous variables and Fisher's exact test for the categorical variables to compare differences between them. The effect sizes (Cohen's *d*) will be calculated to identify differences between the groups; an effect size of 0.2 will be considered a small effect, 0.5 a medium effect, and 0.8 a large effect. As data will be collected from three institutions, generalized estimating equations (GEE), that adjusts standard regression estimators for clustering, will be applied. The primary outcome is the level of psychological distress (BSI). Secondary outcomes' (craving, pain, affect, and aggressive antisocial behaviors) mediating and moderating effect will be also explored by conditional process analyses. We plan to conduct a mid-point analysis (about nine months after that data collection has started) to allow for better modeling of change trajectories.

To describe the adolescents' experiences of participating in yoga practice, with the help of a semi-structured interview guide (Supplementary Material), individual interviews will be performed. The adolescents will be contacted within 2 weeks after completing the yoga intervention. Content analysis will be used as a method for analyzing the interviews (52). The qualitative content analysis is performed stepwise identifying meaning units, condensing the meaning units, labeling meaning units with codes and thereafter identifying subcategories, categories ant themes. Content analysis makes it possible to describe the adolescents' experiences on both manifest and latent levels.

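### GEE clustered on three institutions: with its usual uncorrected variance, the nominal 5% test rejects falsely about 24–32% of the time

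*Protocol article*

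**What the plan says.** The Data Analysis section of the protocol article gives the number of sites as the reason for the method: "As data will be collected from three institutions, generalized estimating equations (GEE), that adjusts standard regression estimators for clustering, will be applied". The Participants section states "Three institutions at the South West in Sweden have at this stage declared interest in participating in the study" and adds that "we will be able to perform intervention and data collection in each participating institute twice, six months apart". The timetable is built on that number: 3 institutions × 2 rounds × 3 months = 18 months, the stated one and a half years.

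The Procedure section lets each young person choose yoga or comparison after the pre-intervention test, so both groups can exist inside every institution. The Data Analysis section names BSI as the primary outcome, applies one threshold throughout ("All statistical analyses will be conducted using a significance level of" p < 0.05), and restricts the data: "Only complete post-attrition data will be analyzed". The same section assigns between-group comparison of continuous variables to Mann–Whitney tests and plans conditional process analyses for mediation and moderation. It names no variance estimator, working correlation, small-sample correction or reference distribution for the GEE.

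**The concern.** What normally makes GEE an adjustment for clustering is its empirical (sandwich) variance, whose justification is that the number of clusters is large. The plan chooses the method because there are three clusters, which is a setting where that justification fails. More participants per institution do not help, because the variance is still estimated from three contributions. Analysing the sexes separately cannot raise the number of institutions either.

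The groups are self-chosen, so a regression is where differences between institutions would be handled. GEE is the only named analysis that takes account of institution. If its standard error is far too small, a significant GEE result carries little weight, although the Discussion hopes that positive results will support national investment.

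**Working it through.** **The plan's own figure.** The sample-size statement is "for two groups (yoga and comparison) and two measurements (pre-and post-intervention) suggested a sample size of 34 for each sex", "with an effect size of 0.25" and power 0.80 at 5%. For the within-between interaction, λ = f²·N·m/(1−ρ) with df (1, N−2). With f = 0.25, m = 2, N = 34 and ρ = 0.5 (not stated, assumed), λ = 0.0625 × 34 × 2 / 0.5 = 8.5 and power is 0.807. The 34 per sex is reproduced. Other values of ρ give N = 66 (ρ = 0), 46 (0.3) or 22 (0.7). The calculation treats participants as independent, so it says nothing about clustering.

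**Inputs for the check.** From the article: 3 institutions, 2 rounds each (at most 6 institution-by-round groups), individual choice of group, 5% level, 34 completers per sex and so 68 in all, about 120 enrolled, and attrition up to 50% (hence also 60 completers, 20 per institution). Assumed, because the article gives no figure: intraclass correlation 0, 0.05 and 0.10, roughly 50:50 uptake, and a two-sided test.

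**Why three is too few.** The sandwich variance is A⁻¹(Σ U_k U_k′)A⁻¹, where U_k is the contribution of institution k. The estimating equations force ΣU_k = 0, so only two of the three contributions are free. As a rough approximation, the estimated variance is low by a factor of 2/3 and the statistic behaves like t on 2 df, for which P(|t₂| > x) = 1 − x/√(2 + x²).

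- Instability alone: x = 1.96 gives 1 − 1.96/√5.842 = 0.189.
- Instability plus bias: x = 1.96 × √(2/3) = 1.600 gives 1 − 1.600/√4.561 = 0.251.

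Hand arithmetic therefore puts the nominal 5% test at about 25%.

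**Simulation with no yoga effect.** Gaussian GEE, institution as cluster, exchangeable correlation, baseline score as covariate, uncorrected sandwich and Wald z at 1.96; 1,000 runs per row-and-column cell:

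| Completers | ICC 0 | ICC 0.05 | ICC 0.10 |
|---|---|---|---|
| 34 | 30.4% | 29.9% | 29.8% |
| 68 | 30.0% | 25.7% | 25.5% |

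Variants at ICC 0.05, 700 runs each:

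- 68 participants: independence working correlation 27.7%; unequal institution sizes and uptake 29.4%; no baseline covariate 26.9%; yoga effect varying by institution (variance 0.05) 29.3%.
- 120 participants: 24.4%.

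The Monte Carlo standard error is about 1.4–1.7 points. Separate simulations with 3 × 20 completers gave 26–31% and 28–32% for the default test, and 24–26% with independence working correlation. Some GEE fits reached the iteration limit. The independence runs, which estimate no correlation parameter, show the same picture.

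**Other ways of carrying out the sentence:**

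| Analysis | False rejection |
|---|---|
| Six institution-by-round clusters, default sandwich z | about 13–20%, depending on the model |
| Three clusters, bias-reduced variance, z | 12.7–14.0% |
| Three clusters, ordinary sandwich, t on 2 df | 8.8–10.1% |
| Three clusters, bias-reduced variance, t on 2 df | 2.2–3.7% |
| Three clusters, model-based GEE errors | 5.4–8.9%; 10.7% if the effect varies by institution |
| Institution fixed effects, t-test | 4.9% at 34 and at 68; about 4–7% over all simulations |

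**Stress test of the fixed-effects model** (3 institutions × 2 rounds × 10, ICC 0.05): effect variance between institutions of 0.05 or 0.10 gives 7.6% or 10.1%. Class-level variance of 0.05 or 0.10 within the yoga arm gives 5.7% or 7.7%.

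**The case against.** The strongest reply is that the article never mentions a robust variance. It says only that GEE adjusts for clustering, and a condensed article may leave the variance estimator and degrees of freedom to a fuller document. A bias-reduced variance with t on 2 df would not inflate the error rate at all. This stands in part: 24–32% describes the method's default, not quoted text. What the article does fix is institution-clustered GEE, chosen because there are three institutions, and most ways of carrying that out miss 5%.

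A reader might infer that the trial's own false-positive rate is one in four. The article does not support that. It also names Mann–Whitney tests for continuous variables and does not say which analysis decides BSI. Nor is GEE the only regression in the plan, since the conditional process analyses are regression-based too, though they are exploratory.

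One might read the clustering as participants with repeated measures. With 68 single-participant clusters the default test gave about 7%, but the sentence ties clustering to institutions.

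It is also fair that fixed effects are not a perfect cure. Yoga is taught in group classes, and the stress test shows rates above 5% when the effect varies by institution or class. Finally, self-selection and completer-only analysis limit causal conclusions whatever standard error is used. That is true, but it does not excuse a wrong one.

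**Conclusion.** The concern holds for the GEE result. With three institutions and the uncorrected sandwich z-test, a nominal 5% test rejects falsely about 24–32% of the time, roughly five to six times the intended rate. With six institution-by-round clusters the rate is about 13–20%. The three-cluster result changes little over an ICC of 0–0.10, 34–120 participants, either working correlation, and equal or unequal institutions. It rests on the default variance and z reference, which the article does not name, and on assumed ICC and uptake. It does not extend to the Mann–Whitney tests or to the trial as a whole.

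**What to change.** Replace institution-clustered GEE with a participant-level regression of the outcome on group, with institution (two indicators) and round (one indicator) as fixed effects and t-based inference on the residual degrees of freedom. The simulations also carried the baseline score as a covariate. State that no uncorrected variance clustered on three institutions will be relied on. Because yoga is chosen individually, the contrast is available within each institution and the model can be fitted.

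If GEE is kept, the only clustered version examined that avoided inflation combines a bias-reduced variance with t on 2 df, and it is conservative (2.2–3.7%). The same paragraph should say whether this model or the Mann–Whitney test decides BSI.

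The cost is wording and three degrees of freedom; no new data or participants are needed. There are two downsides to state. Inference is limited to the participating institutions, which three sites impose in practice. And the error rate is near 5% (about 4–7% in simulation) only if the yoga effect does not vary by institution or class; with assumed variance of 0.05–0.10 it is about 6–10%.

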## Discussion

While there is a growing body of evidence in favor of the unique and significant positive effects of yoga as a form of complementary care for vulnerable populations (such as people with psychiatric conditions and/or people in correctional settings), there is a lack of research measuring the effects of yoga in the population of adolescents in residential/institutional care. The Swedish National Board of Institutional Care (Statens institutionsstyrelse, SiS) offers compulsory care for young people who manifest psychiatric disorders, substance use disorder and criminal behavior (2). The average age of an institutionalized young (fe)male is 16 years old, and (s)he meets the criteria for at least one psychiatric diagnosis. The most frequent diagnoses are ADHD, Substance Use Disorder, PTSD, Conduct Disorder, and Autism Spectrum Disorder. Depression and anxiety are usually co-existing diagnoses. One in four of these young people has attempted suicide. This population of adolescents has an increased need for effective treatments that can prevent the development of persistent mental ill-health, substance dependence, recidivistic criminal behavior, social marginalization, and untimely death. The young people's mental ill-health in SiS is substantial and extensive medical and psychological treatments are provided during their stay. SiS's goal and vision is, that the young people undergoing various SiS treatment programs should have gained by the end of their stay at SiS increased resources to live their lives without crime and abuse.

According to a follow-up study (5) today's institutional care is not sufficiently effective. Half of these young people have a history of at least one inpatient treatment episode, 60% are reconvicted for criminal acts, and 3% die within three years of their release from the institution.

Therefore, the planned study's impact can be measured from the aspects of the individual, the organizations, and the society.

Disruptive behaviors and high levels of psychological distress often hamper treatment responsivity. The suggested positive effects of yoga (decreased levels of psychological distress and less aggressive and antisocial behavior) may result in increased treatment responsivity, which may reduce the number of care days. This positive outcome may entail considerable benefits in terms of significantly decreased economic burdens on SiS and the society.

Reduced recidivism and substance use are not only valuable from a socioeconomic perspective, but they are also necessary for the promotion of a safe society for all and, of course, represent a vital benefit for the individual. The study population comprises a highly relevant group from the perspective of basic societal needs. There are about 550,000 15–19-year-old Swedish citizens today. 0.2% of these adolescents are institutionalized in SiS care yearly (4). The care provided to this small fraction of adolescents represents a considerable annual cost for society (1.6 million SEK/person for medication and 2.1 million SEK/person for placement in SiS care). If this vulnerable group's care and rehabilitation are not successful, it will continue to represent a considerable burden on society at several levels: criminality, medical health problems, social support needs, pain, and suffering of the individual and others.

An active heroin addict costs society 2.1 million and an amphetamine addict about 1.5 million SEK/year from an economic perspective. These figures encompass the expenses for their active use (criminality, legal authorities, and financial aid), medical and social care, and costs for their family's support.

In the event the present study can provide evidence on the positive effects of yoga for the clients of SiS institutions, it will provide a basis and rationale for making a strategic investment at the national level.

The positive effects of yoga at the individual level are proposed from strong scientific evidence. Studies have proven in adult populations that yoga can strengthen the practitioner's self-acceptance, purposefulness, and sense of responsibility (26). These qualities promote a more peaceful and safer environment in institutional settings and offer higher effectiveness of other treatments and school education programs. Yoga can also provide a foundation for the development of a prosocial lifestyle upon release. In other words, there is evidence that yoga empowers the individual yoga practitioner and thus improves his or her mental health and prosocial lifestyle. These novel effects of yoga practice emphasize the importance of testing yoga as complementary care for young people with behavioral and mental health problems.

The duration and the type of yoga in the present study have been adjusted to the population. We use a shorter intervention time but more frequent training (six weeks twice a week, implying 12 yoga sessions) to optimally adapt to the participating institutes' possibilities. Several studies have proven that 8–10 weeks (once a week, therefore, 8–10 sessions) yoga has positive effects on mental health, behaviors, and self-control of adults in correctional setting (9, 25–27, 53). As our study population includes adolescent, it is essential to recognize that the brain goes through pruning (anatomically improving its efficiency) during this developmental period [see e.g., (54)]. During this time, the brain is increasingly susceptible to environmental effects; therefore, we speculate that eventual changes in adolescents' mental health and behaviors will be recognizable already after six weeks (12 sessions) of training. There are results indicating that short-term intensive interventions (four weeks, three times a week yoga classes) have a positive effect on adults' anxiety, depression, and stress (55). Importantly we use a specifically developed yoga (trauma-informed yoga), adapted to the most common psychiatric disorders (ADHD, PTSD, anxiety, and depression) in the adolescent study population.

The proposed study fills a gap in knowledge focusing on young people population in institutional care. If the study's hypothesis is confirmed, our results will verify and strengthen earlier findings in Sweden (9, 25, 26) regarding the benefits of yoga for a marginalized population, thus indicating the usefulness and value of yoga within juvenile institutional care at a national level.

One limitation of the proposed study is the fact that we won't be able to randomly distribute participants between groups, with other words, we could not rationalize a randomized controlled trial (RCT) design. A quasi-experimental design was chosen in agreement with the clinical and institutional experts, who predicted an unacceptable high attrition rate (80–90%) in case of not giving the possibility to the young clients to freely choose their participation in yoga classes.

Future RCTs should confirm our findings and prospective longitudinal studies need to investigate if yoga within SiS can potentially offer a prosocial activity upon release from institutions for young people.

### Ethics and Dissemination

Young people placed in SiS institutions are in many respects in a vulnerable position because of their deprived situation. From an ethical research perspective, therefore, it should be taken into account that this position may affect their propensity to decline to participate in the study due to fear of negative consequences. However, this risk may be considered small. Therefore, great emphasis will be placed on the research ethical principles regarding information, consent, confidentiality, and usefulness. Consequently, all participants will be informed, both orally and in writing, about the purpose and structure of the study, that participation is voluntary, and that they have the right to end their participation at any time. Written consent will be obtained from all study participants before inclusion in the study. All data and information gathered will be treated with the highest possible confidentiality. In this context, it should also be clear from the information that the decision to participate or not in the study, will not affect the young person's treatment plan in any way.

The National Ethical Review Authority has approved the study with the registration number: 2019-04589. We applied for a change in the original ethical approval as we have changed—based on last year's feedback on our grant applications—the study design from RCT to quasi-experimental design, and we included qualitative interviews in the project. The new ethical approval is registered with Dnr: 2021-00088.

This project is carried out in close collaboration with the Swedish National Board of Institutional Care (Statens institutionsstyrelse, SiS), an independent Swedish government agency operating a multidisciplinary activity. The care and treatments offered within SiS institutions must be based on the individual's needs (person-centered care). On a national level, only methods for which there is scientific support are used. Yoga is offered already in some SiS institutions, but not included in care, because of the lack of research and evidence.

The project will take part in University West's academic environment, where the (in Sweden) unique Social Psychiatric Care candidate program is established. The Social Psychiatric Care program covers the interfaces between social services, psychiatric healthcare, the police, correctional centers, schools, and non-governmental organizations. The project is also coupled to the research center for Child and Youth Studies at University West (56), which is part of a network of similar research environments at Stockholm University, Linköping University, University of Gothenburg, and Malmö University. The purpose of the network is to gather and promote research in the interdisciplinary field of child and youth studies.

The project is supported by the Prison Yoga Project (PYP) (57), a non-profit organization that supports incarcerated people worldwide with trauma-informed yoga and mindfulness programs. The PYP Community includes a wide range of professionals (academics, certified yoga instructors, prison employees, medical doctors, etc.) with a common aim to promote social change, transforming the systems and culture to create a more inclusive, equitable, and just world.

Information about the project is disseminated using several channels: producing reports to SiS, open accesses peer-reviewed scientific articles, giving scientific and popular scientific lectures at national and international forums, and using the above-described collaborations.

## Ethics Statement

The National Ethical Review Authority has approved the study with the registration numbers: 2019-04589 and 2021-00088. Written informed consent to participate in this study will be provided of the legal guardian (in case of the participants is under the age of 15) and all the partcipants.
